## 5.2 Methods and procedures

### 5.2.1 Laboratory setting

Ndlovu Medical Centre (NMC) has an on-site basic laboratory which is fully equipped with centrifuge, flow hood, -80 and -120 freezers for storage of samples equipped with digital thermo control system, automatic electrical failure alarm system and reconnection to an alternative power supply in case of power cuts. The laboratory personnel are capable of performing CD4 cell count assays and preparation of dried blood spots.

### 5.2.2 Viral load determination

Quantitative measurement of plasma HIV-1 RNA (viral load) will be determined using a CE/IVD certified kit-based HIV-1 viral load assay, according to the instructions of the manufacturer. Batch wise retrospective analyses will be performed on stored plasma samples of patients with therapy failure in the control arm in order to determine duration of viremia. Results will be reported in copies/ml.

### 5.2.3 Clinical assessment

A clinical assessment will be performed in both arms, in accordance with the recommendations for “Baseline and routine clinical and laboratory assessment for late adolescents” specified in the South African NDoH HIV treatment guidelines. Separate algorithms are followed for baseline and follow-up visits.

- **Baseline clinical and laboratory assessment** consists of WHO clinical staging, screening for symptoms suggestive of infection with *M. Tuberculosis*, other opportunistic infections and symptoms of concomitant chronic diseases and sexually transmitted infections. Screening of laboratory markers is performed to assess contra-indications to components of first-line ART and, if indicated, for detection of AIDS-defining conditions.
- **Follow-up clinical and laboratory assessment** consists of WHO clinical staging, screening for symptoms suggestive of *M. Tuberculosis* infection and other opportunistic infections.

In addition, weight, co-medication, time of medication intake and other events occurring during clinical follow-up will be recorded. Baseline and follow-up assessments will be recorded in a data collection form. Appropriate clinical action will be taken if abnormalities are detected.

Detected abnormalities can form a motivation to perform VL testing outside of the study protocol in conformation with South African NDoH guidelines.

#### 5.2.4 Follow-up of elevated viral load measurement

##### 5.2.4.1 Intervention arm

In case of a VL >1000 copies/ml of a patient in the intervention arm, feedback of this result will be given by the clinical site laboratory after 2-5 working days). The patient will be notified to report back to the research clinician or nurse at his/her next monthly routine clinical visit for medication collection (day 28 after study visit). At this visit repeat viral load testing, DLM and collection of plasma and DBS is performed. If DLM indicates no detectable drug level (see “5.2.5 Drug Level Monitoring”), the patient is informed of this result, and intensified adherence counselling is performed. If DLM does not indicate non-adherence, standard of care adherence counselling will be performed. The result of the second VL will be available after 2-5 working days (day 31-33 after study visit). In case of a second VL >1000 copies/mL and a detectable drug level at DLM, the DBS will be sent to the WHO reference laboratory for drug resistance testing and patients will be notified again to report back to the research clinician or nurse at his/her next monthly routine clinical visit (day 56 after study visit) for genotype guided switch to second-line therapy or for genotype guided continuation of treatment combined with counselling in case no relevant resistance is detected. In case DLM detected no drug level, the DBS is not sent and genotyping not performed. The patient will not be called back and not be switched to second-line therapy prior to the next study visit. In case an elevated VL is again detected at the subsequent study visit (day 84 after previous study visit), a DBS is sent directly for drug resistance testing and genotype guided therapy switch or continuation is performed. In case of continuation, the three monthly monitoring frequency is maintained. In case of switch, a VL will be performed six months after the switch to evaluate initial therapy success. Three monthly study visits will be continued in an observational manner, at which storage of DBS and plasma is performed.

##### 5.2.4.2 Control arm

In case of a VL >1000 copies/ml of a patient in the control arm, VL will be repeated, and intensified adherence counselling will be given during the next routine drug pick-up and counselling visit (2 months after detection). If a second VL is also elevated >1000 copies/ml, switching to second-line therapy is performed and intensified counselling is maintained. If the second VL is <1000 copies/ml, the current regimen is maintained. In case of switch, a VL will be performed six months after the switch to evaluate initial therapy success. Three monthly

study visits will be continued in an observational manner, at which storage of DBS and plasma is performed.

#### 5.2.5 Drug Level Monitoring (DLM)

DLM will be performed in case of a VL >1000 copies/ml at any of the intervention arm study follow-up visits. DLM will take place at a call back visit one month after the visit in which elevated VL was detected, using EDTA-derived plasma obtained at the call back visit. DLM will be performed on-site using a qualitative assay that can be implemented in basic clinical laboratories, and will detect plasma levels of the NNRTI's efavirenz and nevirapine. Results will be reported as either “detectable drug level” or “no detectable drug level”, the latter indicating at least several days of non-adherence over the last week. This result will be reported back to the treating research clinician at the call back visit, who will inform the patient of the result during this visit.

#### 5.2.6 Dried Blood Spot-based Drug Resistance Testing

In case of a confirmed detectable viral load (>1000 copies/ml) in the presence of detectable drug level as indicated by DLM, a dried blood spot (DBS) sample acquired during the second viral load measurement will be sent to a WHO reference laboratory for drug resistance testing, where genotypic HIV-1 drug resistance testing will be performed using an RT-only assay optimized for non-B HIV subtypes. This assay has been validated for use on DBS and implemented in a pilot study at Ndlovu Medical Centre. The assay consists of a single-round one-tube RT-PCR to amplify the viral RT-gene between codons 40-238, followed by population sequencing of the amplified fragment in both directions using 2 primers only. With this approach all RT resistance information relevant to first-line regimens is generated at minimal cost for laboratory reagents, equipment and personnel. If resistance testing is indicated in patients using second line therapy, a protease-only genotypic assay will be performed on the DBS in addition to the RT-only assay. Drug resistance testing will also be performed retrospectively on stored DBS in all patients with therapy failure in the control group, using the same approach as described above. The WHO reference laboratory will provide the treating physician with the result and interpretation of the drug resistance test, containing viral subtype, a list of all mutations, specific indication of relevance of these mutations to drug-resistance, a drug susceptibility ranking using resistance interpretation algorithms, and an overall interpretation with treatment advice taking local availability of antiretroviral drugs into account.

#### 5.2.7 Questionnaires

Questionnaires will be used to measure a variety of parameters relevant to the trial study objectives (see table 2). For data on adherence (e.g. number and reasons of missed doses, reasons and motives for non-adherence), drug toxicity and physical and mental wellbeing, a questionnaire developed by the AIDS Clinical Trial Group (ACTG) will be used. This validated self-report questionnaire has been included in several clinical trials and consists of a baseline and follow-up questionnaire. A modification of the ACTG baseline questionnaire will be used at enrolment, and a shortened version of the ACTG follow-up questionnaires will be used at month 3, 6, 9, 12, 15, 18, 21 and 24 (study end) in both study arms. Data on adherence from the standard pill count form that is applied at each drug pick-up visit (monthly or every 2 months) will also be collected.

Data relevant to the study objectives regarding social and psychological risk factors are partly covered by the ACTG questionnaires. A newly designed questionnaire will be used that will incorporate the sections from the ACTG questionnaires (mental and physical health), NIDS (socioeconomic status and family structure), CHAMP (substance abuse and sexual risk behavior). This questionnaire will contain item scales modified from the ACTG original, matched to local socio-economic and cultural context, as well as record several additional parameters such as stigmatization (Kalichman & Simbayi) and coping abilities (CISS). Data on Quality of life (QoL) of study participants will be used for evaluation of the cost-effectiveness of the trial intervention and will be recorded using the WHO QOL HIV (BREF) questionnaire and EQ5D questionnaire.

In a substudy participants who become lost to follow-up during the trial and who are successfully traced >28 days after a missed clinical visit (as per standard-of-care clinical procedures) are approached for informed consent to perform an additional questionnaire interview during a home visit.

Questions will be bundled in a comprehensive baseline and study end questionnaire (baseline and month 24), and a brief follow-up questionnaire which will be recorded per 3-monthly study visit (month 3, 6, 9, 12, 15, 18 and 21). In lost to follow-up patients who enter the substudy questionnaires will be recorded during a home visit. For a full overview of parameters and questionnaires, see table 2.

Table 2: overview of questionnaire data

| Parameters                                                                                                                         | Time of collection                                    | Source                                                                                             |
|------------------------------------------------------------------------------------------------------------------------------------|-------------------------------------------------------|----------------------------------------------------------------------------------------------------|
| Socio-economic status
- Demographics (1)
- Employment (2)
- Household composition (3)
- Food insecurity (4)            | Baseline                                              | - NIDS wave 3 Adult questionnaire
- NIDS wave 3
- NIDS wave 3
- SAHANES                   |
| Health
- Mental health (5)
- Physical health (6)                                                                             | Baseline & study end                                  | - PHQ-9                                                                                            |
| Transmission factors
- Sexual risk behaviour (7)
- Transactional sex (8)                                                     | Baseline                                              | - CHAMP
- CHAMP                                                                                 |
| Adherence factors
- Attitudes toward therapy (10)
- Stigmatization (11)
- Coping abilities (12)
- Substance abuse (13) | Baseline
Baseline
Baseline
Baseline          | - ACTG Baseline & FU
- Kalichman&Simbayi
- CISS-21
- CHAMP                                |
| Pill counts and self-reported adherence (SoC)                                                                                      | Baseline & every 3 months home visit in LTFU patients | South African NDoH standard of care pill count form                                                |
| Quality of life
- HIV-related QoL
- QoL for QALY valuation                                                                   | Baseline & every 3 months                             | - WHO QOL HIV (BREF)
- EQ5D                                                                     |
| Substudy loss to follow-up (LTFU)
- Outcomes after LTFU
- Patient-reported reasons for LTFU                                  | Phone call & home visit in LTFU patients              | - Wilkinson, Skordis et al (2015)
- Tweya, Feldacker et al (2013)
- Geng, Odeny et al (2015) |

## 5.2.8 Determinants of therapy failure

In all patients peripheral blood mononuclear cells (PBMCs) will be isolated at the baseline study visit, prior to start of therapy. The availability of stored PBMCs and plasma at baseline will enable future study of virological, immunological and pharmacological determinants of therapy failure in those patients in which therapy failure occurs. During study follow-up PBMCs will be isolated every three months in a subgroup of patients. Permission for this sub study will be requested in an amendment to the ethics committee.

## 5.3 Study visits and procedures per visit

### 5.3.1 Visits

In the paragraphs below the activities during the different study visits are described. For every activity, it is listed in **bold** whether the research counsellor, **research nurse** or **research clinician** performs the activity. At least one of these will be fluent in local languages, enabling consultation in native languages in all cases. A full overview of study visits is shown in table 3.

#### 5.3.1.1 Baseline visit

Participants will be enrolled at a regular clinic visit. During this visit, patient informed consent will be obtained by the **research counsellor**. After informed consent a questionnaire interview will be performed by the **research counsellor** who will explain and translate all questions if necessary and who will record all baseline questionnaire data (“5.2.7 Questionnaires”) on a digital system. Blood will be drawn for storage of EDTA-derived plasma, preparation of DBS and isolation of PBMCs (**research nurse**) and a physical examination will be performed (**research nurse or clinician**). Clinical data will be recorded in a data collection form (“5.2.3 Clinical assessment”).

#### 5.3.1.2 Randomisation

At the month 6 study visit, a VL measurement will be performed as part of standard of care. Between the month 6 and month 9 study visit participants will be informed of the VL result and, if applicable, informed of the randomisation procedure and of their randomisation result (see “6.2.3 Randomisation procedure”) by the **research nurse** or **research clinician**. If randomisation criteria are not met, either due to viremia >1000 copies/ml or presence of severe clinical conditions, the patient will be informed of these results and excluded from the study, a health assessment will be performed by the **research clinician**, and the patient will be transferred back to clinical care and offered referral to a health care provider of their choice.

#### 5.3.1.3 Follow-up visits

Study follow-up visits in both arms will occur at month 3, 6, 9, 12, 15, 18, 21 and 24 after initiation of ART or after the last VL measurement. These visits will be planned to coincide with monthly drug pick-up visits to ensure that no extra visits to the clinic are needed. At each visit a follow-up questionnaire interview is held (“5.2.7 Questionnaires”) by the **research counsellor**, a medical and physical examination is performed and blood is drawn for storage of EDTA-derived plasma and preparation of DBS (**research nurse**). In case of clinical symptoms or complications the **research clinician** will be consulted. Clinical data will be recorded (“5.2.3 Clinical assessment”).

#### 5.3.1.4 Call-back in case of elevated viral load

##### *Intervention arm:*

A follow-up VL measurement will be performed, patients will be notified of the result of DLM (**research nurse**) and adherence counselling will be intensified (**research counsellor**) if DLM

and/or pill counts indicated suboptimal adherence. The **research clinician** will be consulted if symptoms are noted by the **research nurse**.

*Control arm:*

A follow-up VL measurement will be performed (**research nurse**) and adherence counselling will be intensified (**research counsellor**) if pill counts indicate suboptimal adherence. The **research clinician** will be consulted if symptoms are noted by the **research nurse**.

#### 5.3.1.5 Call-back in case of second elevated viral load

*Intervention arm:*

If DLM indicated a detectable drug level at the previous visit and relevant drug resistance mutations are present, a second-line regimen will be prescribed during this visit (**research clinician**). In case DLM indicated no detectable drug level, drug resistance testing is not performed, the patient will be notified of the results (**research nurse**) and will again receive additional adherence counselling at the next study visit (**research counsellor**).

*Control arm:*

Patients will be switched to second-line therapy (**research clinician**) and adherence counselling is intensified (**research counsellor**).

#### 5.3.1.6 Immediate tracing after a missed visit

In case of a missed scheduled study visit by a study participant, local standard-of-care clinical retention procedures will initially be followed in both trial arms. Patients receive an SMS test message two days after a missed appointment, a phone call if they do not return after the text message (~4 days after missed visit) and a home visit if they do not respond to the phone call and live within the clinic catchment area (~1-2 weeks after missed visit). If retrieved, they are then counselled to attend the clinic as soon as possible for a study visit.

#### 5.3.1.7 Tracing 28 days after a missed visit

As per clinical standard-of-care, patients who do not return to the clinic within 28 days after a missed scheduled appointment will receive a phone call and questionnaire on current location and contact details and treatment status is administered. If telephonic contact cannot be made a home visit is performed when the patient has consented to this. During home visits the standard of care questionnaire on current location and contact details and treatment status is administered.

#### 5.3.1.8 Immediate tracing after a missed visit

In addition to standard-of-care and if informed consent is given, tracing procedures in study participants are expanded by performing home visits in all participants regardless of successful telephonic tracing, during which an in-depth questionnaire interview on reasons for LTFU and a finger prick for sampling of a DBS is performed.

As per standard-of-care, 90 days after a missed scheduled appointment retention status will be re-evaluated. Patients not returned to the clinic will be contacted telephonically and per home visit in case of no telephonic contact to confirm their current treatment status. At this time point the definite patient study outcome will be recorded.

If not retrieved, a patient will be reported as lost to follow up and excluded if two subsequent study visits are missed and the retention procedure for both visits is unsuccessful. If ART is stopped or interrupted, patients will also be excluded from the study. Study exclusion will in no way compromise access to medical care.

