### 6.7.3 Sample size calculation

Sample size calculation is based on power analyses using selection of resistance as the primary study outcome. The first outcome used for power calculation is the selection of non-polymorphic K65R drug resistance related mutation in HIV reverse transcriptase that is selected by currently used first line therapy at any time during study follow-up. Previously observed prevalence rates of the K65R mutation in HIV-1 subtype C infected patients experiencing therapy failure of a first-line regimen are 70% in LMIC and 17% in developed settings. Using a  $1-\alpha$  of 0.9 and a  $\beta$  of 0.05, the inclusion of 14 cases of failure per arm is needed. Cumulative virological failure (VL >1000 copies/ml) is anticipated to occur in 15% of patients at 12 months after initiation of ART and at 20% at 18 months. Taking into account a loss to follow-up of 10% per year and 20% failure rate, 83 patients are needed per study arm

to detect differences in resistance development as described in literature.

The study is also powered to detect the expected differences in selection of multiple resistance mutations in both arms at month 18 after therapy initiation, derived from a pilot study we performed at Ndlovu Medical Centre. In this study we saw an increase of 2.8 to 4.3 mutations per additional 6-12 months of prolonged therapy. This difference can be detected with 10 patients with therapy failure (59 patients per study arm at an expected failure rate of 20% and 10% loss to follow-up a year).

The third outcome used for power calculation is based on a cross-sectional analysis of a detectable VL >1000 copies/ml at the end of the trial (study month 24). The number of patients with a VL test result above 1000 copies/mL is estimated to be 15% in the control arm and 5% in the intervention arm. Taking into account a loss to follow-up of 10% a year, initial inclusion of 216 patients per arm is required to detect the anticipated difference.

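### Patients who are lost or interrupt ART are excluded after randomisation, the month-24 viral-load comparison is sized on those who remain, and the blood spot taken from traced patients has no stated use

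*Protocol*

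**What the plan says.** Section 5.3.1.8 sets the rule for patients who cannot be brought back: "If not retrieved, a patient will be reported as lost to follow up and excluded if two subsequent study visits are missed", provided retention has failed for both visits. The next sentence applies exclusion to anyone whose ART is stopped or interrupted.

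The same section adds a home visit, with consent, at which "an in-depth questionnaire interview on reasons for LTFU and a finger prick for sampling of a DBS is performed". It also has a definite study outcome recorded 90 days after the missed appointment. Section 5.2.7 places these visits in a substudy of participants who were lost and then traced more than 28 days after a missed visit, but describes the consent as covering a questionnaire interview only. Table 2 lists outcomes after loss and patient-reported reasons for it.

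On the blood spot (DBS), section 5.2.6 says of the genotyping assay: "This assay has been validated for use on DBS and implemented in a pilot study at Ndlovu Medical Centre". The stated uses of DBS genotyping are the intervention algorithm, therapy failures, and the pre-ART baseline sample (5.1.2, 5.1.3, 5.2.6). Viral load is specified on plasma (5.2.2). Table 4 has no column for the home-visit sample, and section 6 does not mention it.

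The third power calculation in 6.7.3 concerns VL >1000 copies/ml at month 24, with the proportion "estimated to be 15% in the control arm and 5% in the intervention arm". It concludes: "Taking into account a loss to follow-up of 10% a year, initial inclusion of 216 patients per arm is required to detect the anticipated difference".

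**The concern.** The strategy under test acts on non-adherence. Loss to follow-up and interruption of ART are plausibly consequences of non-adherence, so these exclusions remove, after randomisation, patients in the state that the intervention is meant to change. The trial is open-label. One arm has three-monthly viral loads with drug-level testing after a raised result; the other has yearly viral loads and no drug-level testing. Who is lost, and whose interruption is noticed, could therefore differ by arm. Risks and relative risks among those who remain need not be those of the groups as randomised.

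A later analysis plan can choose an imputation method, but it cannot recover follow-up that the protocol ends by excluding the patient. Meanwhile the trial draws a sample from some of the lost without saying what it is for.

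**Working it through.** **Inputs.** 600 randomised, 300 per arm (4.2, 5.1.2, 5.1.3); 18 months of follow-up after randomisation (4.1); loss 10% a year and month-24 risks of 15% and 5% (6.7.3). Viraemia among the lost is given nowhere, so every value for it below is an assumption.

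**1. The plan's own figure.** Alpha and power are printed only for the first calculation, as "Using a $1-\alpha$ of 0.9 and a $\beta$ of 0.05", apparently transposed. Read as alpha 0.05 (two-sided assumed) and power 0.90, without continuity correction:

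n = [1.96·√(2·0.10·0.90) + 1.2816·√(0.15·0.85 + 0.05·0.95)]² / 0.10² = 187.1, so 188 evaluable per arm.

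Loss over 18 months is 1.5 × 10% = 15%, and 188 × 1.15 = 216.2, which matches 216. Dividing instead gives 188/0.85, or 222. Some other combinations of settings come to 215, so the match is not unique, but this one uses the trial's own duration and loss rate. The 216 is thus a number of observed patients inflated for loss.

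**2. Lost patients against events, at 300 per arm.**
- Lost: 0.15 × 300 = 45 per arm, 90 in all (88 if the loss is compounded).
- Observed: 255 per arm.
- Expected viraemic among the observed: 0.15 × 255 + 0.05 × 255 = 38.25 + 12.75 = 51.
- At 216 per arm: 65 lost against 37 events.
- With 20% loss (24 months) at 300 per arm: 120 lost against 48 events.

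Patients excluded for interrupting ART while still attending are not counted here.

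**3. Effect on the comparison.** With viraemia q among the lost, risk in an arm = 0.85 × (risk among observed) + 0.15 × q.

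| Assumed q, control / intervention | Control | Intervention | Difference | RR |
|---|---|---|---|---|
| same as observed (15% / 5%) | 15.0% | 5.0% | 10.0 points | 0.33 |
| 50% / 50% | 0.1275 + 0.075 = 20.25% | 0.0425 + 0.075 = 11.75% | 8.5 points | 0.58 |
| 30% / 60% | 0.1275 + 0.045 = 17.25% | 0.0425 + 0.090 = 13.25% | 4.0 points | 0.77 |
| 60% / 30% | 0.1275 + 0.090 = 21.75% | 0.0425 + 0.045 = 8.75% | 13.0 points | 0.40 |

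In the 50% / 50% case, power with all 300 per arm is 81%, against 97% for the 255 per arm observed.

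**4. Gap needed to remove the effect.** Difference = 0.85 × 0.10 − 0.15 × g, where g is intervention minus control viraemia among the lost. It is zero at g = 0.085/0.15 = 0.567, about 57 points (40 points at 20% loss).

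**The case against.** The strongest reply is that a completers-only analysis is never stated. Inflating recruitment for loss does not define an analysis set, and exclusion in 5.3.1.8 can be read as ending participation, since the passage goes on to access to medical care. Analysis sets and imputation are commonly left to the statistical analysis plan, which is not at hand. This stands in part: a reader might infer that the protocol commits to dropping these patients from the analysis, and the text does not go that far. What remains is that it orders an exclusion after randomisation and does not say that the patients stay in the analysis.

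A second reply also stands. A reader might infer that the home-visit DBS could supply the missing month-24 outcomes. It cannot. It comes only from consenting patients who are traced, whereas exclusion for loss applies to those not retrieved. It is taken after a missed visit, not at month 24. The assay validated on DBS is for genotyping, and no viral-load test on DBS is specified. There is some overlap with the excluded: 5.2.7 classes the visited participants as lost, and a traced patient found to be off ART is excluded all the same.

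Third, status after loss is not ignored: a 90-day outcome is recorded and Table 2 lists outcomes after loss. But section 6 gives neither a place. Tables 2 and 4 might not be expected to list a substudy assay, and a laboratory manual exists that is not shown, so their silence is weaker evidence than that of section 6.

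Fourth, month-24 viral load is the third of three powered outcomes and is not listed in 6.1; 6.7.3 names selection of resistance as primary. This limits the weight of the figures, although resistance is equally unobserved in patients whose follow-up has ended.

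**Conclusion.** The concern holds in limited form. The protocol excludes, after randomisation, patients whose exit is plausibly tied to the intervention's target, sizes the month-24 comparison on those who remain, and gives no use for a sample taken from some of the lost.

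On the plan's own rates the lost (about 90) outnumber the expected events among the observed (about 51). That is not an error in itself; it shows how far the result depends on unobserved patients. With equal viraemia among the lost, the relative risk moves much more (0.33 to 0.58 at an assumed 50%) than the difference (10 to 8.5 points).

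A reader might go further and infer that loss would probably erase the effect. The documents do not support that: the 4.0-point result needs an assumed 30% v 60% split, the reverse split gives 13.0 points, and removal needs a gap of about 57 points. The direction of any bias is unknown.

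**What to change.** - In 5.3.1.8, state that exclusion for loss or for interrupting ART ends study visits only, and that these participants stay in the randomised analysis population.
- In 5.3.1.8 and 6.1, state that the home-visit DBS from consenting traced participants is genotyped with the DBS-validated assay already in use, and that its result and the 90-day outcome are reported by arm.
- Add a tipping-point or multiple-imputation sensitivity analysis for month-24 VL >1000 copies/ml, informed by these data. Details can sit in the statistical analysis plan.
- Do not let the DBS stand in for the month-24 viral load. Use a DBS viral-load result only if a suitable assay is specified.
- Bring the substudy consent in 5.2.7 into line with 5.3.1.8 so that it covers the blood sample.

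The cost is a few dozen extra assays on samples already planned, and short edits to the protocol and consent. Because the sample covers only consenting traced patients and is not taken at month 24, it supports a sensitivity analysis and not the main one.
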